### 2.6 Secondary outcome measures

The secondary outcome measures are as follows: number of headache days six and nine months after finishing intervention (follow-up) (data derived from diaries); change in consumption of analgesics or triptans (data derived from diaries); change in pain intensity (data derived from diaries); changes in depression, anxiety scores (data derived from tests); increase in pain acceptance (data derived from tests); changes in quality of life (data derived from tests); changes in number of sick-leave days (data derived from the national e-health system); and assessment of impact on the burden of migraine through sick-leave days, disability rate, and specialist visits (data derived from e-health systems). Specific methods are presented in Table 1 and Table 2.

**Table 1 pdig.0000295.t001:** Methods used in the study.

Indicator	Method	Time	Procedures for use	Patient time for filling test	Investigator
Frequency of headaches	Digital diary, paper diary	Continuous	Continuous	> 2 minutes	Patient independently in the application or on paper
Medication use	Digital diary, paper diary	Continuous	Continuous	> 2 minutes	Patient independently in the application or on paper
Medication use	Prescription Centre	Continuously/Intervals ^1^	Continuously/Intervals ^1^	N/A	Specialist desktop/doctor or nurse.
The effect of headaches on everyday life	Headache Impact Test (HIT-6) [53]	Intervals ^1^	Intervals ^1^	2–5 minutes	The patient performs independently in the application or the test environment REDCap.
Screening for mental disorders	Emotional State Questionnaire (ESQ-2) [54]	Intervals ^1^	Intervals ^1^	2–5 minutes	The patient performs independently in the application or the test environment REDCap.
Mental disorders	Diagnostic and Statistical Manual of Mental Disorders, Fifth Edition (DSM-V) symptom checklist + Psychiatrist consultation (if DSM-V symptom checklist detects a mental health disorder	Intervals ^3^	Intervals ^3^	60 minutes	The patient performs independently in the application or the test environment REDCap and/or one psychiatrist appointment
Personality profile	Swedish Universities Scales of Personality (SSP) [55]	Once at the beginning of the study	Once at the beginning of the study	30 minutes	The patient performs independently in the the test environment REDCap.
Pain acceptance	Chronic Pain Acceptance Questionnaire-Revised (CPAQ-R) [56]	Intervals ^3^	Intervals ^3^	2–5 minutes	The patient performs independently in the application or the test environment REDCap.
Pain-related anxiety	Pain Anxiety Symptoms Scale (PASS) [57]	Intervals ^3^	Intervals ^3^	2–5 minutes	The patient performs independently in the application or the test environment REDCap.
Quality of life	EUROHIS-QOL 8-item index [58]	Intervals ^2^	Intervals ^2^	2–5 minutes	The patient performs independently in the application or the test environment REDCap.
Patient satisfaction with treatment	Headache Attributed Lost Time (HALT) [59, 60], Headache Under-Response to Treatment (HURT) [59]	Intervals ^3^	Intervals ^3^	2–5 minutes	The patient performs independently in the application or the test environment REDCap.
Patient satisfaction with digital therapy	Satisfaction questionnaire	Intervals ^3^	Intervals ^3^	>2 minutes	The patient performs independently in the application or test environment REDCap.
Specialist satisfaction with digital treatment methods	Satisfaction questionnaire	Intervals ^3^	Intervals ^3^	> 2 minutes	The specialist performs independently in the test environment REDCap.
Cost-effectiveness	Queries from the statistical databases of the Estonian Health Insurance Fund, the Social Insurance Board, and the Institute for Health Development	Intervals ^2^	Intervals ^2^	N/A	Health economist
Patient’s willingness to pay for headache treatment	Willingness to pay bidding game	Intervals ^2^	Intervals ^2^	2–5 minutes	The patient performs independently in the application or the test environment REDCap.
Demographics	Demographic Questionnaire	At the beginning of the study	Once at the beginning of the study	> 2 minutes	The patient performs independently in the application or the test environment REDCap.

^1^At intervals—at the beginning of the study, at 8-week intervals, at the end of the study

^2^At intervals—at the beginning of the study, at the end of the study

^3^At intervals—at the beginning of the study, at the end of the study, in a follow-up study

**Table 2 pdig.0000295.t002:** The data collected by testing in all groups.

Method	Collected data
Participant demographics	Gender, age, place of residence, nationality, education, marital status, employment, income
Emotional State Questionnaire (EST-Q) test results	Subscales for depression, generalised anxiety disorder, panic disorder, insomnia, and asthenia
Diagnostic and Statistical Manual of Mental Disorders, Fifth Edition (DSM-V) symptom checklist results	Depression, anger, mania, anxiety, somatic symptoms, suicidal ideation, psychotic symptoms, sleep problems, memory problems, compulsive thoughts and behaviors, dissociation, personality dysfunction, and drug use
EUROHIS QOL-8	Quality of life, satisfaction with health, satisfaction with the ability to do everyday life activities, satisfaction with oneself, satisfaction with personal relationships, satisfaction with living conditions, is there enough energy for daily activities, is there enough money to meet one’s needs
Headache Impact Test (HIT-6)	Effect of headache on patient life
Headache Attributed Lost Time (HALT)	Loss of time due to headache
Headache Under-Response to Treatment (HURT)	Response to treatment
Pain Anxiety Symptoms Scale (PASS)	Pain-avoiding behavior, frightening thoughts, cognitive anxiety, physiological reactions to anxiety
Chronic Pain Acceptance Questionnaire-Revised (CPAQ-R)	Participation in activities, pain tolerance, pain acceptance
Swedish Universities Scales of Personality (SSP)	Somatic trait anxiety, psychic trait anxiety, stress susceptibility, lack of assertiveness, impulsiveness, adventure-seeking, detachment, social desirability, embitterment, trait irritability, mistrust, verbal trait aggression, physical trait aggression
Willingness to pay questions (WTP)	Willingness to pay for headache treatment
Patient Satisfaction Questionnaire	Satisfaction with mobile application; Satisfaction with mobile application design (UI); Satisfaction with patient mobile application user experience (UX); Satisfaction with patient mobile application structure; Satisfaction with patient mobile application possibilities; information about the extent to which the mobile application facilitated the subject’s communication with the specialist; satisfaction with digital treatment compared to conventional treatment; whether digital treatment interventions could completely replace conventional treatment; whether the patient wants to continue using the patient application; what suggestions are made to improve the application; what other features patients want to see in the mobile application
Specialist Satisfaction Questionnaire	Satisfaction with the specialist desktop; whether the desktop makes work easier; satisfaction with the specialist desktop design (UI); satisfaction with specialist desktop user experience (UX); satisfaction with the logic of specialist desktop; satisfaction with specialist desktop possibilities; whether the desktop facilitates communication with patients; whether the digital intervention has improved patient satisfaction with the service; what suggestions are made to make the desktop better; what other features you want to see in the mobile app

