Key issues with digital solutions include the absence of real-time therapist/patient interaction, challenges in delivering personalized and timely feedback, difficulties in TBI delivery, regional variability in digital solution availability, issues in generating patient intervention reports or summaries, data protection concerns and potential data loss due to technical, internet connection, programme compatibility, software or hardware issues [12,27,40].

Managing headaches involves a multifaceted approach, encompassing pharmacological and NI treatments, preventative methods, lifestyle changes, and self-monitoring [41,42]. Previous research indicates that users often discontinue digital CBT early, facing challenges in maintaining adherence without sufficient clinical contact [43,44]. Studies on internet-based CBT for depression highlight the impact of depression severity on dropout rates, necessitating continuous monitoring [45]. Future research should explore the influence of anxiety and depression on the treatment adherence of a headache patient. Furthermore, it is unknown whether evidence-based digital therapies can successfully be used outside of clinical practice (i.e., self-help with minimal or no clinical intervention) [41,44].

The effectiveness of DHDs compared to conventional ‘paper-pencil’ headache diaries (PD) remains uncertain, and their impact on treatment adherence is unclear. In conventional diaries, patient often pre-fill fields or mark the conditions later [46–48]. Previous studies indicate that factors such as age, gender, season, day of the week, headache frequency, headache severity, headache medication use, and DHD completion time may all influence a adherence to diary filling [47]. Identifying the elements, background factors and reminders influencing DHD completion is crucial for this study.

Future studies on digital interventions should focus on quantifying the impact of digitally mediated behavioral interventions on pain intensity and psychiatric symptoms. No research has determined the ‘optimal dose’ of behavioral interventions, including the required number and duration of CBT sessions [44]. The effectiveness and successful digital application of evidence-based CBT with minimal clinical involvement also require investigation.

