### 2.10 Interventions

NI conducted with the participants are detailed in Table 4. All materials sent to participants through the Migrevention Clinical solution (study group) or explained in a face-to-face appointment (control group) are based on the intervention manual and are the same in both groups. The discussion topics and materials are distributed in the order specified in the intervention manual. Since the study attempts to mimic a standard conventional intervention as closely as possible, in the case of conventional treatment (control group), the communication between the specialists and participants is not precisely described in the intervention manual, leaving each specialist free rein over communication.

**Table 4 pdig.0000295.t004:** Interventions by group.

	Study group (digitally mediated NI)	Control group (conventionally mediated NI)
Headache diary	Participant is filling DHD in the Migrevention Clinical mobile application.	Participant is filling PHD, usually used in conventional treatment.
Headache nurse counselling	The headache nurse sends self-help materials (previously recorded audio) to the participant through the Migrevention Clinical specialist dashboard and communicates with the patient through the chatroom connected to the Migrevention Clinical mobile application. The Participant receives notifications to the Migrevention Clinical mobile application about new tasks, listens to the materials, and if needed, asks the headache nurse additional questions via the chatroom. Communication through the chatroom is not limited.	The headache nurse arranges face-to-face meetings with the participant to provide conventional nurse counselling. Meetings take place only at agreed times.

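### Change in analgesic and triptan use is defined from diaries whose format follows the arm, while the listed Prescription Centre source is tied to no outcome

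*Protocol article*

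**What the plan says.** Section 2.6 lists as a secondary outcome "change in consumption of analgesics or triptans (data derived from diaries". The same sentence assigns other outcomes to other sources: sick-leave days, for example, come from the national e-health system. The paragraph closes with a general pointer: "Specific methods are presented in Table 1 and Table 2".

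Table 1 has two rows for medication use. The first gives "Digital diary, paper diary" as the method, completed by the patient alone. The second gives "Prescription Centre", read continuously or at intervals, with access through "Specialist desktop/doctor or nurse". Footnote 1 defines the intervals as study start, every 8 weeks and study end.

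The diary format is fixed by arm. Table 4 says of the study groups "Participant is filling DHD in the Migrevention Clinical mobile application", and of the control groups "Participant is filling PHD, usually used in conventional treatment". Table 3 confirms this for all four pairs of groups.

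Section 1 (Background) states that "In conventional diaries, patient often pre-fill fields or mark the conditions later". It also says that how digital diaries perform against paper ones is uncertain, and it names medication use among the factors that may affect how well a diary is kept. Section 2.2 describes the study as open-label and says that the digital format permits reminders.

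**The concern.** In every digital-versus-conventional comparison, the arms differ in treatment and also in the instrument that counts doses. Randomisation does not separate the two, and none of the models named in section 2.11 can, because no digital group uses paper and no control group uses the app. If recording differs between formats, part of the difference in recorded drug use may come from the diary and not from the patient.

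For this outcome, unlike headache days, Table 1 lists a second source that does not depend on the patient keeping a diary. As section 2.6 is worded, no outcome uses it. At stake is whether a statement that digital care spares, or fails to spare, acute medication can be believed.

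**Working it through.** The plan gives no figure for this outcome: no expected use, SD or diary completeness. Its only usable number is the group size in section 2.3, 75 per group, and 8 × 75 = 600 agrees with the stated maximum. Pooling four groups per side would give 4 × 75 = 300, but the article does not say that groups will be pooled.

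**When does a recording difference matter?** Let B and F be true use at baseline and follow-up, the same in both arms.

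- *Constant additive error a:* recorded change = (F + a) − (B + a) = F − B. It cancels, even if a differs by format.
- *Constant proportional capture c:* recorded change = c(F − B). The arms differ by (c_digital − c_paper)(F − B), which is not zero if use truly changes.
- *Capture that changes over time:* recorded change = c_F·F − c_B·B. The arms can differ even if true use does not change.

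**Illustration.** Assumed, not in the documents: B = 8 and F = 6 days per month in both arms, SD of recorded change 3 to 5, two-sided α = 0.05, and the capture rates below. SE = SD·√(2/n), x = |difference|/SE, and the rejection probability is 1 − Φ(1.96 − x) + Φ(−1.96 − x).

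Worked case: digital capture falls from 90% to 80% and paper stays at 90%. Digital: 0.8 × 6 − 0.9 × 8 = −2.4. Paper: 0.9 × 6 − 0.9 × 8 = −1.8. Difference −0.6. With SD 4 and n = 75, SE = 4 × √(2/75) = 0.653, x = 0.919, and the probability is 0.151.

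| Capture, baseline → follow-up | Digital change | Paper change | Digital − paper | False result, 75 v 75 | False result, 300 v 300 |
|---|---|---|---|---|---|
| both 90% throughout | −1.8 | −1.8 | 0 | 5% | 5% |
| digital 95%, paper 80%, constant | −1.9 | −1.6 | −0.3 | 7–9% | 11–23% |
| digital 90→80%, paper 90% | −2.4 | −1.8 | −0.6 | 11–23% | 31–69% |
| digital 90→70%, paper 90% | −3.0 | −1.8 | −1.2 | 31–69% | 84–99.8% |
| paper 90→80%, digital 90% | −1.8 | −2.4 | +0.6 | 11–23% | 31–69% |
| paper 90→70%, digital 90% | −1.8 | −3.0 | +1.2 | 31–69% | 84–99.8% |

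Ranges run over SD 3 to 5. The last two rows mirror the two above them: if paper recording declines, the control groups look drug-sparing. In the fifth row a real extra digital reduction of 0.6/0.9 = 0.67 days would be masked, because 0.9 × 0.67 = 0.6.

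**The case against.** **The second source may already be intended.** Section 2.6 points to Table 1, where the Prescription Centre stands under the same indicator, and a full protocol or analysis plan, not shown, could give it a role. That is possible. But section 2.6 names diaries explicitly for this outcome and names a registry elsewhere in the same sentence where one is meant. A general pointer does not override an explicit source.

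**The source is not shown to be ready or arm-neutral.** This stands. Access is partly through the specialist desktop, which section 2.7 describes as built for the digital intervention, so retrieval could itself differ by arm. Footnote 1, unlike footnote 3, does not mention the follow-up study, and the primary time point is three months after the intervention ends (section 2.5). No prescription window before baseline is described.

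**Prescriptions measure something else.** This also stands. A reader might infer that the triptan outcome should be redefined as units dispensed, with the diary count demoted. The documents do not support that. The stated outcome is consumption, and prescription records show supply. The article does not say whether dispensing is recorded or whether triptans are obtained mainly on prescription.

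**The size is assumed.** A reader might infer that paper diaries are less complete, or that the high percentages above are expected error rates. Neither follows. The Background speaks of pre-filled and late entries, not of lower completeness, and gives no rate of decline for either format. The largest percentages need the largest drift, the smaller SDs and a pooled comparison that the article does not specify.

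**It is one secondary outcome.** True, and the same confounding affects headache days, which a prescription source cannot repair.

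**Conclusion.** The point holds as a modest, low-cost improvement. As written, section 2.6 rests the analgesic and triptan outcome on an instrument that is fully confounded with arm, in a protocol that itself calls the comparison of the two instruments uncertain, and it leaves a listed second source without a role.

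The direction of any bias is unknown: it may favour either arm or conceal a true effect. It requires a recording difference that is proportional to use or changes over time. The size cannot be derived from the documents. The illustration shows only that a ten-point drift in one format is enough to raise the false-result rate above 5%, and that a constant proportional difference does much less (7–9% at 75 per group).

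The documents do not show that the Prescription Centre could replace the diary. They support its use as a check on the triptan part.

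**What to change.** In section 2.6:

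1. Keep the diary outcome, and report triptans and other analgesics separately.
2. Pre-specify a supporting analysis of triptans prescribed or dispensed (state which the Prescription Centre records) per randomised patient.
3. Extract these data in the same way for all eight groups, not through the digital-arm desktop, over equal-length windows before baseline and up to the primary time point.
4. Make any drug-sparing conclusion depend on the diary and the Prescription Centre agreeing for triptans, and say in advance what counts as agreement.

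Cost: outcome wording and one uniform extraction from a source that Table 1 already lists, with no added patient burden. It must first be confirmed that the extraction can cover both windows, since the article does not say so; if it cannot, the cost is higher.

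Limits: prescription records show supply, not intake, and may miss drugs bought over the counter. The check is useful only so far as triptans are obtained on prescription, which is an assumption. The headache-day primary outcome remains exposed to the same confounding.

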### 2.7 Patients inclusion and specialists involvement process

The neurologist examines the eligibility of the patient for the study, explains their opportunity to join the study, and presents an informed consent form. Within three business days, the study team contacts the patient, provides answers to any patient questions, asks patients to sign the informed consent form digitally, and conducts a randomization. Subjects are divided among eight groups according to randomization, and the treatment intervention continues according to the manual.

For digitally administered intervention, a separate desktop (Migrevention Clinical specialist dashboard) will be developed for the specialists, which is accessible via the work computer of the specialist and is cross-linked to the mobile application of the patient (Migrevention Clinical). Specialists who treat participants via the Migrevention digital solution are assigned a separate working time and a so-called remote reception time.

The usual clinical face-to-face contact during conventional treatment intervention occurs as a regular consultation according to a detailed intervention plan.

Clinical face-to-face contact during a digital treatment intervention occurs through video consultation if a specialist recognizes the urgent need for it (for example, the depressive and/or anxiety scores of the patient increase).

### 2.8 Settings and randomization process

The study will be conducted in parallel for each intervention setting—the four study groups (digital treatment groups) and the four control groups (standard interdisciplinary treatment groups or treatment standard groups) (Table 3).

**Table 3 pdig.0000295.t003:** Division of groups.

Study group I	Control group I	Study group II	Control group II	Study group III	Control group III	Study group IV	Control group IV
UMT^1^	UMT	UMT	UMT	UMT	UMT	UMT	UMT
DHD^2^	PD^3^	DHD	PD	DHD	PD	DHD	PD
		DHN^4^	UHN^5^	DHN	UHN	DHN	UHN
				dCBT^6^	uCBT^7^	dCBT	uCBT
						dPT	uPT

^1^UMT–Usual Minimal Treatment

^2^DHD–Digital Headache Diary

^3^PD–Paper Diary

^4^DHN–Digital Treatment by Headache Nurse

^5^UHN–Usual Treatment by Headache Nurse

^6^dCBT–Digital CBT Programme

^7^uCBT–Usual CBT Programme

^8^dPT—Digital Physiotherapy

^9^uPT–Usual Physiotherapy

After the initial informed consent, patients who qualify for the study will be added to the research group and assigned a participation number based on the precise time the study group acquired the contact information of the patient (date and time, if necessary). After the informed consent is signed, participants are randomized into eight groups. A randomization table has been created for this purpose, in which 600 distinct numbers are randomly separated into eight groups. The patient is assigned to a group in accordance with the randomization table.

All groups receive the usual minimal treatment consisting of medications in addition to the usual appointment with a neurologist. Control groups receive the usual treatment consisting of medications, the usual appointment with a neurologist, headache nurse, CBT therapist and a physiotherapist, in different combinations. All ‘as usual’ treatments involve clinical face-to-face contact.

All participants of the study groups receive digital treatment consisting of medications and a neurologist appointment as usual. Additionally, each participant is assigned digital appointments with the following specialists: headache nurse, CBT therapist and/or physiotherapist. These appointments are assigned in different combinations depending on the randomization. The digital interventions are delivered through the Migrevention Clinical solution.

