## 3. Discussion

Designed by an interdisciplinary team, our research aims to compare digitally mediated NI migraine treatment options with conventional ones, determine the optimal approach for enhancing patient health and quality of life, optimizing specialists’ time, and extending assistance to more migraine patients.

A notable strength of this study is its status as a prospective randomized controlled study of a novel, standardized, manual-based intervention that focuses on, among other things, monitoring compliance and compares fully digital intervention with conventional interdisciplinary NI. Another strength of the study is the assessment of the efficacy and applicability of each treatment component separately, in addition to the whole treatment protocol.

The authors hope that the study helps to overcome the challenges in the field of digital therapeutics (DTx) [62]. The study provides an opportunity to begin to determine the effectiveness of DTx in the treatment of migraine. The implementation of the project also contributes to the integration of DHD data with the e-health system so that they are usable for all providers (including general practitioners) as well as the connection of DHDs to electronic health records.

Interdisciplinary intervention in migraine treatment is known to be effective, especially in preventing migraine chronification [63]. Given the high risk of migraine chronification, long-term treatment adherence and follow-up may be essential to ensure the long-term effectiveness of digital interventions [64]. Based on the above, the research plans to conduct long-term follow-up studies (3, 6, 9 months after the end of the intervention).

There are some limitations that may affect the conduct and results of the study and must be considered when interpreting the results in the future.

The initial sample size will see at least 75 patients in each group, according to the Power analysis. Due to the time-consuming conventional interventions and the time needed to collect data, the realistic obtainable group size within the given timeframes of the study may be smaller. The study may favour the larger clinics and research centers for adopting the protocol and conducting the study and limit similar possibilities of smaller centers. In order to overcome this problem, interim analyses can be undertaken to examine statistically significant associations in a smaller number of patients.

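### As written, the randomization procedure does not protect allocation concealment: the number rests on contact time, before signature, and the only allocation key described is a pre-made number table

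*Protocol article*

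**What the plan says.** Section 2.7 of the protocol article describes recruitment. The neurologist checks eligibility, then "explains their opportunity to join the study, and presents an informed consent form". Within three business days the study team contacts the patient, answers questions, "asks patients to sign the informed consent form digitally, and conducts a randomization". All of these steps are given to one team.

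Section 2.8 describes numbering and allocation. On numbering: "After the initial informed consent, patients who qualify for the study will be added to the research group", and they are "assigned a participation number based on the precise time the study group acquired the contact information of the patient". On allocation: "After the informed consent is signed, participants are randomized into eight groups". On the list: "A randomization table has been created for this purpose, in which 600 distinct numbers are randomly separated into eight groups". On the rule: "The patient is assigned to a group in accordance with the randomization table".

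The trial is open-label (section 2.2), and the primary outcome, the reduction in headache days, comes from diaries (section 2.5). Sections 2.9 and 2.12 mention REDCap for completing tests and storing data, not for allocation.

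**The concern.** Concealment means that nobody who can influence whether a patient enters the trial can foresee that patient's group. The usual safeguard is that nothing linking the patient to an allocation exists until consent and eligibility are irrevocably recorded. Here the number rests on an event that comes before the call and the signature, and the allocation list already exists. If the two are linked, the group is settled during the very conversation in which the patient decides whether to join.

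Neither patients nor treating staff are blinded, and patients keep the diaries that supply the primary outcome. Concealment at entry is therefore one of the main protections left. If it fails, groups can differ in prognosis before treatment begins, and no later analysis fully repairs that.

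**Working it through.** The point concerns procedure, so the main check is the order of events.

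**Figure in the plan.** Section 2.3 gives 75 patients in each group, and there are eight groups: 8 × 75 = 600. This agrees with the 600 numbers in the table, so the table holds exactly one number per planned participant.

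**Order of events, from sections 2.7 and 2.8**

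1. The neurologist checks eligibility and presents the consent form. No signature is described at this visit.
2. The study group receives the contact details. The time of receipt is the basis of the participation number.
3. The study team contacts the patient and asks for a digital signature. This has to follow step 2, because the team cannot make contact without the details.
4. After signature, the group is read from the table made in advance.

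The basis of the number (step 2) therefore precedes the signature (step 3).

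**Is the participation number the key to the table?** Section 2.8 does not say so in words. It describes a participation number, then a table of distinct numbers, then assignment by the table, and it names no other key. The plain reading is that they are the same number.

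**When is the number issued?** Section 2.8 places numbering after an initial informed consent and randomization after consent is signed. If these are two stages, the number is issued before signature. If both mean the signature, the number is issued afterwards, but its value still rests on the earlier contact time.

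**Does randomizing after signature help?** It fixes when the table is consulted. If number and table both exist beforehand, the result could have been read beforehand as well.

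**Illustration only.** None of these inputs is in the documents. Suppose someone able to foresee the group loses a share q of the worse-prognosis half of candidates in one group only, and prognosis correlates r with the outcome. The mean of that half is 0.798 SD from the centre (normal distribution), so the bias in SD units is

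b = r × 0.798 × 0.5q / (1 − 0.5q).

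For one pair of groups of 75, the standard error is √(2/75) = 0.163 SD. The true two-sided error rate at nominal 5% then follows from shifting the test statistic by b/0.163.

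| r | q | b (SD) | True error rate |
|---|---|---|---|
| 0.3 | 0.1 | 0.013 | 0.051 |
| 0.5 | 0.2 | 0.044 | 0.058 |
| 0.5 | 0.5 | 0.133 | 0.129 |
| 0.7 | 0.5 | 0.186 | 0.207 |

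The range runs from negligible to serious, depending wholly on the assumed r and q. It shows why the size cannot be stated.

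**The case against.** The strongest reply is that this is a condensed article. Custody and release of the list are commonly left to the full protocol, so silence on them proves nothing. That stands. A reader might infer that allocation is in fact not concealed, and the documents do not support this: nothing says who holds or can see the table.

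A second reply is that the participation number may be only an identifier, with a table row drawn separately after signature. The text permits this. A reader might therefore go too far in saying that the number already maps to a group. For the same reason one cannot conclude that candidates who decline use up rows, so that the table runs out before 600 enrol and power falls. That needs both the unstated link and numbers issued before signature.

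Third, the opportunity is limited. The neurologist judges eligibility before the study team makes contact, section 2.3 specifies consecutive patients, and the person taking consent does not choose the arrival time. The exposure lies between receipt of contact details and signature. This narrows the concern but does not remove it, since that interval is when the patient decides.

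Fourth, a reader might take the Discussion as evidence that staff have reason to steer patients away from face-to-face groups. It says only "Due to the time-consuming conventional interventions and the time needed to collect data, the realistic obtainable group size within the given timeframes" may be smaller. It does not describe any pull to discourage candidates.

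What survives is not an argument from silence. The article sets out a specific mechanism: a number based on a pre-consent event, a ready-made table, and one team for contact, consent and randomization. A fuller document could restrict access to the table, but the number would still rest on an event before signature.

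**Conclusion.** The point holds in this form: the procedure as written does not protect allocation concealment. Three elements are in the text: numbering by contact time, a pre-made table as the only allocation key described, and one study team that contacts, consents and randomizes. That a patient's group is determined while consent is open depends on the participation number being the table's key, which is the plain reading but is not stated. The initial consent stage is also ambiguous. Confidence is therefore moderate.

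The documents do not allow the resulting bias to be sized. The plan gives no SD, effect size or rate of non-signing, and the table above is illustration only. The point deserves correction on the sequence alone, because selection before enrolment cannot be undone afterwards.

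**What to change.** - Separate the identification number from the randomization number. The first may keep following contact time; the second must not depend on it.
- Release the next unused row of the table only after signed consent and eligibility have been recorded.
- Make the release through REDCap, if its randomization function is available, or through a list holder not involved in recruitment.
- State that those who contact and consent patients cannot see the table.
- Log the time of signature and the time of release for each participant.
- For candidates already numbered under the contact-time rule, report how many did not sign, by pre-assigned group. If the participation number was never the table's key, say so and state what was.

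The cost is a short amendment and set-up work in REDCap, or some time from a list holder outside recruitment. The sample size need not change.
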